### Outcome

A proforma will be developed by the researcher which will be used to document the demographic features (such as age, weight, height, blood pressure, address, type of incontinence, education status, and marital status) of all the participants as well as the pre, post and follow-up intervention findings of the study.

### Primary outcome measure

The primary outcome measure is urine leakage, and it will be assessed using the 1-h clinic pad test. The 1-h clinic pad test is an effective, simple, noninvasive, valid, and reliable method recommended by the International Continence Society for quantifying the amount of urine loss that will aid in the diagnosis/quantification of urinary incontinence, as well as assessing the efficacy of certain procedures that are used in the management of incontinence [38, 39]. The procedure for the pad test will be in line with the recommendation of the International Continence Society. Each participant will be asked to empty their bladder before the test, and drink 500 ml of water. A pre-weighed Always-Ultra pad will be given to the participant to place inside her underwear. The participant is then asked to sit for 15 min. After this, the researcher will instruct the participant to cough 10 times, squat 10 times, jump up and down on the spot 10 times, and walk briskly for 10 min. After 1-h, the pad will be removed and re-weighted using the Grams weighing scale. To quantify urine leakage, the difference in the pad weight will be calculated by subtracting the original pad weight from the pad weight after 1 h. A 1 g gain in pad weight will be considered as proof of UI, and a reduction in urine leakage to < 1 g after the intervention will be considered as a cure.

### Secondary outcome measures

The secondary outcome measures are Pelvic Floor Strength (PFS) to be measured using a perineometer; QoL to be measured using the Incontinence Quality of Life questionnaire; SF to be measured using the Female Sexual Function Index (FSFI); and Mental Health (MH) to be measured using the Hospital Anxiety and Depression rating scale (HADs). The perineometer is a highly reliable instrument used in assessing PFS with high intraclass correlation coefficient values of 0.95 and 0.88 for strength, and 0.94 and 0.83 for endurance, which indicate high within-day and between-days reliability for PFM strength and endurance respectively [42]. The PFS will be assessed according to standard protocol [42]. Each participant will be asked to lie supine with knees semi-flexed; the probe of the perineometer will be inserted into the vagina until the full extent of the compressible portion of the device is at the level of the hymen. Each participant would then be instructed to maximally contract her PFM by trying to pull her pelvic floor in and up as much as possible (as if trying to stop urine from coming out) for 2–3 s. The researcher will observe the participant to ensure that she is breathing normally. Three squeezes will be recorded at intervals of 10 s between the efforts, and the average will be recorded in cms/H_2_O as the maximum perceived strength of the PFM; the higher the reading the higher the PFS [21].

The Incontinence QoL questionnaire is a valid and reliable questionnaire used to assess QoL with excellent internal consistency (Cronbach’s value of 0.93 and 0.79–0.89) and has no ceiling effect [43]. It is a 22 item self-reported disease-specific questionnaire that assesses the effect of UI on QoL under three (3) subscales of Avoidance and Limiting Behaviour (ALB), Psychosocial Impact (PSI), and Social Embarrassment (SE) [28, 43]. Specifically, the ALB subscale consists of 8 items, the PSI consists of 9 items, and the SE consists of 5 items. Moreover, scores ranging from 1 (extreme) to 5 (not at all) will be used to grade each of the items, and the total scores (for the 22 items) will then be transformed to a “scale score” ranging from 0 to 100 using the following formula:$${\text{Scale}}\,{\text{score}} = {\text{Sum}}\,{\text{of}}\,{\text{the}}\,{\text{items}}{-}{\text{Lowest}}\,{\text{possible}}\,{\text{score/Possible}}\,{\text{raw}}\,{\text{score}}\,{\text{range }} \times 100.$$Higher scores from all the items indicate less impact of PFRI on QoL [28, 43].

The Female Sexual Function Index (FSFI) is a questionnaire used in the assessment of female sexual function. The questionnaire possesses good psychometric properties (high test–retest reliability for each domain r = 0.79 to 0.86, and high internal consistency (Cronbach’s values of 0.82 and above) and it is easy to administer [44]. It is a multi-dimensional questionnaire with 19 items that are self-reported for assessing SF in women. It comprises six (6) domains: desire, subjective arousal, lubrication, orgasm, satisfaction, and pain. The desire domain has 2 items with scores ranging from 1 to 5 in each item, summed up to a total score of 2 (minimum) and 10 (maximum); the arousal domain has 4 items with scores ranging from 0 to 5 in each item, summed up to a total of minimum and maximum scores of 0 and 20 respectively; the lubrication domain has 4 items with scores ranging from 0 to 5 in each item, summed up to a total of minimum and maximum scores of 0 and 20 respectively; the orgasm domain has 3 items with scores ranging from 0 to 5 in each item, summed up to a total of minimum and maximum scores of 0 and 15 respectively; the satisfaction domain has 3 items with scores ranging from 1 to 5 in each item, summed up to a minimum and maximum score of 2 and 15 respectively; and the pain domain has 3 items with scores ranging from 0 to 5 in each item, summed up to a total of minimum and maximum score of 0 and 15 respectively. An FSFI total score of less than or equal to 26.55 indicates risk for sexual dysfunction.

The Hospital Anxiety and Depression rating scale (HADs) will be used to assess mental health (MH). It is a valid and reliable questionnaire used in determining the mental status of an individual [45]. Each participant will be asked to complete the HADs after clear and detailed explanation by the researcher on how to complete the questionnaire. The HADs comprises seven questions for anxiety and seven for depression and it takes 2–5 min to complete. The anxiety and depression questions are combined in the scale; however, it is recommended that they are scored separately [46]. Both scales demonstrate good to moderate to high internal consistency; Cronbach's alpha for anxiety varied from 0.68 to 0.93 (mean 0.83) and for depression from 0.67 to 0.90 (mean.82) [45].

## Data analysis

Microsoft Excel will be used to record all the data obtained before being exported to the Statistical Package for Social Sciences (SPSS). Descriptive and inferential statistics will be used to analyse the data. All study parameters will be summarized using descriptive statistics of frequency, mean, standard deviation, and percentage. Factorial ANOVA will be used to determine between-group differences/interactions in the study groups from the pre to the follow-up study period for PFS and UL among study participants. The Wilcoxon signed-rank test will be computed to determine differences between the pre, post and follow-up intervention for SF, ML and QoL scores in both the experimental and control groups. The independent t-test will be used to determine the difference in the post intervention PFS and UL scores between the experimental and control groups, while Mann–Whitney U will be used to determine the difference in the post intervention for SF, ML and QoL scores between the experimental and control groups. The magnitude of the differences between the groups will be determined by calculating the effect sizes. Missing data will be handled through multiple imputation. All analyses will be performed with probability set at 0.05 alpha level.

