**Methods:**

This is a study protocol for a randomized controlled trial. A total of 182 participants are expected to participate in the study after satisfying the inclusion criteria. The participants will be randomized into either PEM or PFMT study groups. The demographic data of all the participants will be recorded. Each participant will be assessed for urine leakage, PFS, QoL, SF, and MH at baseline and subsequently, at four, eight and 12 weeks of intervention.

Demographic parameters will be summarized using descriptive statistics. Continuous data will be computed for differences using inferential statistic of Analysis of variance, t-test and Man Whitney U as appropriate. All analyses will be performed using SPSS version 22.0 with probability set at 0.05 alpha level.

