## Methods

### Study design and sample

The research design for this study is a randomized controlled trial (RCT). It is a quantitative research in the form of pretest, posttest and follow-up design. The study will be a two-arm, outcome assessor-blinded RCT. The two-arms will comprise an intervention and a control. Following participants’ consent and baseline assessments, eligible participants shall be allocated randomly into either the intervention group (Paula exercise method) or the control group (pelvic floor muscle training). The proposed timeline for this study is 12 calendar months from participants’ enrolment to follow-up assessments; Table 1 below:

**Table 1 Tab1:** Study timeline from enrolment to completion

	Enrollment	Allocation	Post-allocation				Follow-up
Time point	− t	0	t0 (0 week)	t1 (4 weeks)	t2 (8 weeks)	t3 (12 weeks)	t4 (6 months)
Enrollment: eligibility screen informed consent allocation	X						
	X						
		X					
Intervention: Paula exercise (experimental group) Pelvic floor muscle training (control group)			X	X	X	X	
			X	X	X	X	
Assessments: baseline variables—age, weight, height, blood pressure, marital status, educational status, post fistula repair time	X	X					
Assessments: outcome variables [Primary outcome- urine leakage] [Secondary Outcome- pelvic floor strength, quality of life, sexual function, depression and anxiety]			X	X	X	X	X

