### Data collection procedure

This study has been approved by the Human Research Ethics Committees of Kano State and Jigawa State Ministries of Health.

Assessment of all participants will be carried out in four stages (at baseline, at 4 weeks, at 8 weeks, and at the end of the study). A comprehensive assessment of the participants will be conducted, where personal demographic information (age, height, weight, marital status, educational status) and PFRI-specific information (time since VVF repair, type/size of the VVF, amount of urine leakage) will be assessed at baseline; and functional status information (QoL, MH, SF, and PFS) will be assessed at baseline and after every four weeks up to 12 weeks. All the parameters will be assessed during follow-up after 6 months.

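### The ANOVA planned for urine leakage and pelvic floor strength names no within-woman term and takes baseline as a response level; run literally, it misstates both of its tests

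*Protocol article*

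**What the plan says.** The Data analysis section assigns one method to leakage and pelvic floor strength over time: "Factorial ANOVA will be used to determine between-group differences/interactions in the study groups from the pre to the follow-up study period". The abstract is less specific: "inferential statistic of Analysis of variance, t-test and Man Whitney U as appropriate". Neither place, nor any other, names a repeated-measures factor, a subject term or a sphericity correction.

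Table 1 (Study design and sample) marks "Primary outcome- urine leakage" and the secondary outcomes at 0, 4, 8 and 12 weeks and at 6 months. The Data collection procedure describes four assessment stages and adds "All the parameters will be assessed during follow-up after 6 months". The Study design and Randomization sections place baseline assessment before allocation.

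Two other sentences in the Data analysis section bear on the point. A paired method is named for the questionnaire outcomes: "The Wilcoxon signed-rank test will be computed to determine differences between the pre, post and follow-up intervention for SF, ML and QoL scores". A one-value-per-woman comparison is also planned: "The independent t-test will be used to determine the difference in the post intervention PFS and UL scores between the experimental and control groups". The section sets alpha at 0.05 for all analyses and does not say which of the ANOVA and the t-test is primary.

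**The concern.** A plain factorial ANOVA of group by time has a single error term, pooled over all observations. When the same women supply every visit, that term is wrong for both tests of interest. The group effect is tested as if each visit came from a different woman, so it rejects too often. The group-by-time effect is a within-woman comparison tested against an error that still contains the variation between women, so it rejects far too rarely and loses power.

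The analysed period also starts at the pre-treatment assessment. That visit becomes a level of the response although the expected difference between arms there is zero.

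The primary outcome is involved. A chance group effect could be reported as the trial's finding, or a real difference in course over time could be missed.

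**Working it through.** **Inputs.** From the protocol article: 83 evaluable women per arm (Sample size), five assessments (Table 1) and alpha 0.05, taken as two-sided because the side is not stated. The within-woman correlation ρ is not given, so it is assumed over 0.2 to 0.8 with equal correlation between visits and variance 1. The number of visits T that enter the ANOVA is not stated, so T = 5 and T = 3 (pre, post, follow-up) are both shown. The plan gives no error rate or power for this ANOVA, so there is no figure of its own to reproduce; its sample size calculation is for a Mann-Whitney test.

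**1. Group effect, literal reading.** The difference in arm means averaged over T visits has variance (2/nT)·[1 + (T−1)ρ]. The between-subjects ANOVA assumes 2/nT. Hence

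type I error ≈ 2·[1 − Φ(1.96/√(1 + (T−1)ρ))].

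For T = 5:
- ρ = 0.3: 1.96/√2.2 = 1.32, giving 0.19
- ρ = 0.5: 1.96/√3.0 = 1.13, giving 0.26
- ρ = 0.7: 1.96/√3.8 = 1.01, giving 0.31

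For T = 3 the error runs from 0.10 (ρ = 0.2) to 0.22 (ρ = 0.8).

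**2. Group-by-time, literal reading.** Under the null the interaction mean square has expectation 1 − ρ, against an error mean square of 1. Hence

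type I error ≈ P(χ² on T−1 df > c/(1−ρ)), with c = 9.49 for T = 5.

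This gives 0.009 (ρ = 0.3), 0.0008 (ρ = 0.5) and below 0.0001 (ρ = 0.7). For T = 3 it runs from 0.023 (ρ = 0.2) to below 0.0001 (ρ = 0.8).

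**3. Simulation check** (5,000 null trials, 83 per arm). At T = 5 and ρ = 0.5, rejection was 0.264 for group and 0.001 for interaction. Lognormal data, closer to the skewed leakage of the pilot, gave 0.218 and 0.003.

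**4. Mixed (split-plot) reading, T = 5, ρ = 0.3 to 0.7.** Type I error was 0.049 to 0.051 for group and 0.044 to 0.054 for interaction. With correlation decaying over visits (first-order autoregressive, 0.7), the uncorrected interaction rose to 0.073.

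**5. Baseline as a response level.** If the effect is 0.5 SD at all four post-baseline visits and zero at baseline, the averaged group effect is (0 + 4 × 0.5)/5 = 0.4 SD. This is dilution, not error inflation. Leaving baseline out of the literal ANOVA still gave a group type I error of 0.22 at ρ = 0.5.

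**6. Power for 0.5 SD from week 4 on, T = 5** (2,000 simulated trials; 83 per arm gives about 90% power for this effect by a two-sided t-test):

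| Test | ρ = 0.3 | ρ = 0.5 | ρ = 0.7 |
|---|---|---|---|
| Literal ANOVA, group-by-time | 0.58 | 0.52 | 0.47 |
| Mixed ANOVA, group-by-time | 0.79 | 0.92 | >0.99 |
| Mixed ANOVA, group | 0.97 | 0.91 | 0.84 |
| Baseline-adjusted ANCOVA, week 12 | 0.92 | 0.95 | 0.99 |
| t-test, week 12 | 0.89 | 0.89 | 0.89 |

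The week-12 t-test held a type I error of 0.048 to 0.052 and the ANCOVA 0.044 to 0.054.

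**The case against.** The strongest objection is that the plan never says visits are treated as independent. A group-by-time design examined for interactions can equally be a mixed factorial ANOVA. The authors choose a paired test for the questionnaires, so they know that these are same-woman data. A condensed article may also leave the error term to a fuller document. This stands. A reader might infer that the plan definitely counts each woman's five measurements as five women; the text does not settle that, and the figures of 19% to 31% apply only to the literal reading.

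A reader might also infer that including baseline itself makes the error rates wrong. It does not: step 5 shows that the inflation remains without baseline, and in a mixed ANOVA the group-by-time test with baseline as a level is valid.

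Five visits is Table 1's number and not the Data analysis section's. With three, the inflation is smaller but in the same direction.

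Finally, the post-intervention t-test is sound on this point. It does not remove the problem, because the plan does not rank it above the ANOVA and both are tested at 0.05. Nor does the mixed reading leave nothing to correct, since dilution of the main effect and the need for a sphericity correction remain.

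**Conclusion.** The concern holds conditionally. As worded, the method for the primary outcome admits two readings.

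- **Between-subjects ANOVA.** The group effect is anti-conservative: about 19% to 31% with five visits and ρ of 0.3 to 0.7, and about 10% to 22% with three visits and ρ of 0.2 to 0.8. The interaction is very conservative: below 1% with five visits and ρ of 0.3 to 0.7.
- **Mixed ANOVA.** Type I error is about 5% under sphericity. What remains is a diluted group main effect, a power loss that is modest at ρ = 0.5 (0.91 to 0.92 against 0.95 for baseline-adjusted ANCOVA), and a sphericity correction for the interaction.

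The correlation is an assumption throughout, and the power figures assume a constant 0.5 SD effect from week 4. On either reading a better analysis is available from the data already planned, so the wording should be changed before analysis.

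**What to change.** Replace the factorial ANOVA for leakage and pelvic floor strength with a repeated-measures linear mixed model (MIXED in SPSS):

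- the woman as the unit, with a stated within-woman covariance;
- post-baseline visits only as outcomes;
- the baseline value as covariate;
- group, visit and group-by-visit as fixed effects.

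Report the group contrast with its 95% CI at one named primary visit, for example week 12, the end of the intervention. State that this contrast is the primary analysis and that the t-test is supportive.

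Because leakage is skewed and pad gain can be zero, use a transformation defined at zero, such as log(x + 1), or add a robust or rank-based check.

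The cost is analysis wording only. Visits, data, software and sample size are unchanged, and the planned multiple imputation can stay.

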### Sample size

The sample size of this study was estimated based on the findings of a pilot study. We conducted a pilot study to test the adequacy and feasibility of this protocol as well as to determine the sample size required for this study. The pilot study participants were recruited after being certified as eligible to participate using the specified study inclusion criteria. Recruitment was conducted by reviewing records of the outpatient urology clinic on a weekly basis. A total of 30 women with post fistula repair incontinence participated in this pilot study. The 30 subjects were randomly assigned into the two arms of the study resulting into 15 participants in each arm of the pilot study (Paula Exercise Method and Pelvic Floor Muscle Training groups). All participants were assessed at baseline before randomization and prior to the commencement of intervention, post intervention (outcome). The primary outcome of interest is Urine leakage. The programme was structured for 4-weeks of daily routine activities in both groups. The detail of urine leakage assessment is described later in the manuscript as the primary outcome measure.

In this pilot study the mean age of participants was 29.9 ± 9.4, the median Urine leakage score for PEM and PFMT was 4.53 g and 21.61 g respectively. We computed Mann Whitney U for the data because the data was not normally distributed. Result for an independent two groups non-parametric test indicated significance (*U* = 38.00,* p* = 0.020) with an effect size of *Ƞ*^2^ = 0.32.

Using the outcome of the pilot study and according to a power calculation to detect a between-group difference, of 0.3 effect size for two independent means Mann Whitney U in urine leakage (UL) with 90% power at α = 0.05, a total sample size of 166 was generated. This suggests a total of 83 participants in each group. A 10% attrition rate will be considered, therefore, 182 participants will be recruited giving 91 participants in each group. The recruitment of participants from the two hospitals would be accomplished by: involving the surgeons from the departments of obstetrics and gynaecology of both hospitals who are involved in performing the fistula repairs (in the recruitment); and reviewing hospital registry and subsequently contacting patients whose records are available through individual phone contacts.

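### The primary outcome is assigned a t-test and ANOVA on raw pad-test grams, although the pilot found it non-normal and the sample size rests on Mann-Whitney, so the stated 90% power does not belong to the planned test

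*Protocol article*

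**What the plan says.** Primary outcome measure section: urine leakage is the weight gain of a pad over one hour, in grams. It is defined as "the difference in the pad weight will be calculated by subtracting the original pad weight from the pad weight after 1 h". No logarithm or other transformation is mentioned there or in the analysis section.

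Sample size section: in the 30-woman pilot, "the median Urine leakage score for PEM and PFMT was 4.53 g and 21.61 g respectively". The choice of test is explained: "We computed Mann Whitney U for the data because the data was not normally distributed". The main trial is then sized for "0.3 effect size for two independent means Mann Whitney U in urine leakage (UL"), with 90% power at an alpha of 0.05. This gives 166 women (83 per group), raised to 182 for attrition.

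Data analysis section: "Factorial ANOVA will be used to determine between-group differences/interactions in the study groups from the pre to the follow-up study period for PFS and UL", and then "The independent t-test will be used to determine the difference in the post intervention PFS and UL scores between the experimental and control groups". The same section keeps Mann-Whitney for the post-intervention comparison of sexual function, mental health and quality of life. All study parameters are to be summarised by "descriptive statistics of frequency, mean, standard deviation, and percentage", a list without the median that the pilot used for this outcome.

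**The concern.** The sponsor judged pad-test grams unsuitable for a normal-theory test in the pilot and planned the trial size around a rank test. The analysis section then puts the same variable on the parametric side and the questionnaires on the rank side.

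Two things are at stake. First, power stated for one test does not carry over to another when the data are skewed. Pad weights start at zero and can have a long right tail, so a few heavy leakers may dominate the mean and SD. Second, the tests answer different questions: the t-test compares mean grams, while Mann-Whitney compares the ordering of the two distributions. They can disagree on the primary outcome, and the article gives grounds for either.

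**Working it through.** **1. The conflict, side by side**

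| Item | Sample size section | Data analysis section |
|---|---|---|
| Distribution of leakage | not normal (pilot) | not discussed |
| Summary | median | mean and SD |
| Between-arm test | Mann-Whitney | t-test and factorial ANOVA |

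**2. What the pilot implies about spread**

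The article gives no SD or skewness, so a model is needed. Assume log-normal grams with the same log-SD σ in both arms.

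- Inputs (Sample size section): U = 38, 15 per arm, medians 4.53 g and 21.61 g.
- Share of the 15 × 15 = 225 pairs in which the PFMT woman leaks more: 1 − 38/225 = 0.831.
- Under the model this share equals Φ[ln(21.61/4.53) / (σ√2)].
- ln(21.61/4.53) = 1.562 and Φ⁻¹(0.831) = 0.959.
- σ = 1.562 / (1.414 × 0.959) = 1.15.

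The pilot's own figures do not fully agree. With 15 per arm, U has null mean 112.5 and SD √(225 × 31/12) = 24.11. U = 38 therefore gives z = (38 − 112.5)/24.11 = −3.09 and p = 0.002, not the reported 0.020. Eta-squared is 3.09²/30 = 0.32, which matches. If p = 0.020 were the correct figure instead, the same steps would give σ of about 1.64.

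**3. Shift that gives Mann-Whitney 90% power at 83 per arm**

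Two-sided 5%, using the rank test's efficiency of 3/π on the log scale:

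δ = (1.960 + 1.282) × √[(2/83) × (π/3)] = 0.515 log-SDs.

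The ratio of medians is exp(0.515σ), which is 1.81 at σ = 1.15.

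**4. Simulated power, log-normal grams, 83 per arm, 8,000 trials per row**

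| log-SD | Ratio of medians | Mann-Whitney | t-test on raw grams |
|---|---|---|---|
| 0.25 | 1.14 | 90% | 90% |
| 0.5 | 1.29 | 90% | 87% |
| 0.75 | 1.47 | 90% | 82% |
| 1.0 | 1.67 | 90% | 74% |
| 1.15 | 1.81 | 90% | 69% |
| 1.5 | 2.16 | 90% | 54% |
| 2.0 | 2.80 | 89% | 37% |

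Repeat runs moved these by about one point, hence about 70% at 1.15 and a range of about 38% to 91%. The Welch version gives the same figures within a point. A t-test on log(grams + 1) keeps about 91%. A log-SD of 1.64 would fall between the last two rows.

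**5. A different skewed shape**

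Take gamma-distributed grams, also bounded at zero and right-skewed, that differ in scale, with Mann-Whitney at about 89%. The raw t-test then has 98% (shape 0.5), 96% (1), 94% (2) and 92% (4). There is no loss.

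**6. Type I error of the raw t-test, log-normal, no true difference**

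4.3% (log-SD 1.15), 3.5% (1.5) and 3.2% (2.0).

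**7. The 90% starting point**

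Read as a standardised difference, an effect of 0.3 with two-sided 90% power needs 468 women in total for a t-test, or 492 for Mann-Whitney on normal data. At 83 per arm, power would be 49% or 47%. The article does not name the effect-size metric, and 166 does not follow from 0.3 on this reading. Steps 3 and 4 therefore take 90% as stated, not as verified.

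**The case against.** A reader might infer that the trial simply loses much of its planned power. The documents do not support that. It needs a distribution that they do not give, and the sign of the effect depends on it: log-normal data favour the rank test, gamma data with a scale difference favour the t-test, and mild skew makes little difference. If the true effect were as large as the pilot's (a median ratio of 21.61/4.53 = 4.8), either test would have about 100% power at log-SD 1.15, and the raw t-test would still have 94% at 1.5, though only 64% at 2.0.

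A reader might also infer that the t-test would be invalid on these data. It would not: at 83 per arm it stayed at or below its nominal error rate in the simulations. Mean grams lost is also a legitimate target in its own right.

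Finally, the abstract says that ANOVA, t-test and Mann-Whitney will be used as appropriate. That signals some flexibility, but the analysis section allocates each outcome by name and puts leakage under the t-test. If the abstract did override it, the primary test would be left open, which would be no better.

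These objections limit the claim about size. They do not remove the conflict between the two sections.

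**Conclusion.** The mismatch is certain from the text: the primary outcome is tested by a method that fits neither the pilot finding nor the basis of the sample size, so the 90% power is not a statement about the planned analysis. Because the article names a test in both places, this is a contradiction and not a detail left to an analysis plan.

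The consequence for power is conditional. The figure of about 70% rests on equal-variance log-normal grams, the log-SD of 1.15 derived from a 30-woman pilot, and a shift fixed at Mann-Whitney's 90%. The range within that family is wide, and another plausible family shows no loss. Confidence is high on the contradiction and low on its size.

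**What to change.** Name one primary between-arm analysis of urine leakage, at one stated time point, that matches the sizing. There are two candidates:

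- **Preferred:** a model on log(grams + 1), adjusted for baseline log leakage, with the effect reported as a ratio and 95% CI. It accepts zero values, extends to the repeated visits (weeks 4, 8 and 12 and 6 months), and works with the multiple imputation already planned.
- **Alternative:** Mann-Whitney with the Hodges-Lehmann difference and 95% CI. This is the test named in the sizing, but it needs a separate solution for the repeated visits and for imputed data. If the effect is multiplicative, there is no constant gram shift for the Hodges-Lehmann estimate to describe.

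Then take leakage out of the raw-scale t-test and ANOVA sentences, summarise it by median and quartiles, and restate the power for the chosen test with the effect-size metric named.

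The wording cost is a few sentences, to be settled before unblinded data are examined. The effect will no longer be a mean difference in grams; raw means can still be shown descriptively. Restating the power takes more work, because 166 has to be re-derived and may not be confirmed.

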### Randomization

After screening the participants, and following baseline assessments, a computer-generated random allocation sequence will be used to assign the participants to either the intervention group (PEM group where they will receive PEM plus PFMT), or the control group (where they will receive PFMT only). To eliminate bias, the randomization will be carried out by a third party who is not aware of the study group. Assessment of outcome will be carried out by an experienced/trained researcher, who will be blinded to the type of intervention received by participants in each group. The study participants’ flow diagram is presented in Fig. 1

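### The post-intervention between-arm tests leave out the pre-randomization baseline, and for sexual function, mental health and quality of life no between-arm test uses it

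*Protocol article*

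**What the plan says.** The Data analysis section names four procedures.

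- **UL and PFS, post scores, between arms:** "The independent t-test will be used to determine the difference in the post intervention PFS and UL scores between the experimental and control groups".
- **Sexual function (SF), mental health (printed as ML) and quality of life (QoL), post scores, between arms:** a Mann-Whitney U test that "will be used to determine the difference in the post intervention for SF, ML and QoL scores between the experimental and control groups".
- **UL and PFS over time:** a factorial ANOVA to "determine between-group differences/interactions in the study groups from the pre to the follow-up study period for PFS and UL".
- **SF, mental health and QoL within each arm:** "The Wilcoxon signed-rank test will be computed to determine differences between the pre, post and follow-up intervention for SF, ML and QoL scores".

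The section adds: "Missing data will be handled through multiple imputation". No covariate-adjusted model is named.

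Baseline values will exist for all five outcomes. The abstract's Methods paragraph states: "Each participant will be assessed for urine leakage, PFS, QoL, SF, and MH at baseline". Table 1 shows the same set of outcomes at week 0, and Data collection procedure says that QoL, mental health, SF and PFS "will be assessed at baseline and after every four weeks up to 12 weeks". Randomization places these measurements before allocation: "After screening the participants, and following baseline assessments, a computer-generated random allocation sequence will be used".

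**The concern.** A baseline measured before randomization cannot be affected by treatment, so it is a legitimate covariate. It usually predicts the later score. A test on post scores alone leaves that predictable variation in the error term, and the estimate is less precise than it could be with the same women and the same visits.

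For SF, mental health and QoL there is a second problem. Baseline is used only inside each arm, by the signed-rank test. Both arms do an active exercise programme, and Randomization describes the Paula exercise method (PEM) arm as also receiving pelvic floor muscle training (PFMT). Improvement within the PEM arm therefore says nothing by itself about what PEM adds. A result that is significant in one arm and not in the other invites that conclusion.

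**Working it through.** **Inputs.** From Sample size: 83 per arm before attrition, α = 0.05, 90% power, effect size 0.3 with no metric named. From Data analysis: the tests listed above. Assumed, because the document does not give them: a baseline-to-post correlation r of 0.3, 0.5 or 0.7; normal data with equal variance at both times; two-sided testing; a standardized difference d = 0.5.

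**The plan's own figure.** If 0.3 is read as a standardized difference, n per arm = 2(1.960 + 1.282)²/0.3² = 233.5, so 234 per arm and 468 in total for a two-sided t-test. The stated 166 is not reproduced. With 83 per arm, 90% power corresponds to d = (1.960 + 1.282)·√(2/83) = 0.503. That is why d = 0.5 is used below. It is an assumption and not a figure from the protocol. The sample-size mismatch is a separate matter and does not decide this point.

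**Gain over the post-only t-test.** Adjustment multiplies the residual variance by 1 − r², so the effective d becomes d/√(1 − r²). Power is from the noncentral t distribution.

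| r | 1 − r² | Variance cut | Effective d | Power, post-only t | Power, adjusted |
|---|---|---|---|---|---|
| 0.3 | 0.91 | 9% | 0.524 | 89.3% | 91.9% |
| 0.5 | 0.75 | 25% | 0.577 | 89.3% | 95.9% |
| 0.7 | 0.51 | 49% | 0.700 | 89.3% | 99.4% |

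The factor 1/(1 − r²) is 1.10, 1.33 and 1.96, so the adjustment is worth about 10%, 33% or 96% more women.

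At d = 0.3 (normal approximation), power would go from 48.9% to 52.6%, 60.7% or 77.2%.

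**Gain over the factorial ANOVA (UL and PFS).** With two time points, the group-by-time interaction is a comparison of change scores, with variance 2(1 − r) times the single-score variance. The ratio of ANCOVA to change-score variance is (1 − r²)/[2(1 − r)] = (1 + r)/2 = 0.65, 0.75 and 0.85. ANCOVA is the more precise at every r below 1. Simulated power at d = 0.503, 83 per arm, 4,000 runs:

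| r | Post-only t | Post-only Mann-Whitney | Interaction | ANCOVA |
|---|---|---|---|---|
| 0.3 | 90% | 89% | 78% | 93% |
| 0.5 | 89% | 88% | 89% | 96% |
| 0.7 | 90% | 89% | 98% | 99% |

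Below r = 0.5 the interaction is weaker than ignoring baseline altogether. The text does not say that time is a repeated factor. If visits were treated as independent, interaction power in the same simulation would be 67% to 72%.

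**Within-arm tests.** Suppose both arms truly change by the same amount and each signed-rank test has power p. Exactly one arm is then significant with probability 2p(1 − p): 50% at p = 0.5, 32% at 0.8, 18% at 0.9. With anxiety and depression scored separately, as Secondary outcome measures recommends, there are up to 2 arms × 4 scores × 3 pairs of times = 24 such tests, none of which compares the arms.

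**The case against.** **Baseline is not absent from every between-arm analysis.** A reader might infer from the post-score tests that no comparison of the arms uses it. That is wrong for the primary outcome and for PFS, because the factorial ANOVA runs from the pre-intervention to the follow-up period. At r = 0.7 that analysis already reaches 98% power against 99% for ANCOVA, so for UL and PFS most of the gain over the t-test would disappear. This stands. It leaves the gap at lower correlations, and it does not help SF, mental health and QoL, which the ANOVA does not cover.

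**This is a choice about efficiency and not an error.** Allocation is random, so post-score tests are unbiased and keep their type I error. Chance imbalance at baseline is variation that they already allow for. This stands too. A reader who inferred bias would be going beyond the document.

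**The within-arm misreading is not planned.** Each questionnaire outcome has its own Mann-Whitney test between arms, and nothing says that a PEM effect will be concluded from the signed-rank results. That is fair. The risk lies in how the results will be read.

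**The figures are illustrative.** Both r and d are assumed, and the power calculations use normal data, whereas Sample size reports that pilot leakage was not normally distributed. The size of the gain for skewed leakage and questionnaire scores is therefore uncertain. Its direction is not in doubt when baseline predicts outcome.

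**Multiple imputation does not rule out rank tests.** A reader might think that the two cannot be combined. They can: U/(n₁n₂) estimates the probability of superiority and has a standard error. An adjusted model is simpler to pool, but that is a convenience and not a defect in the plan.

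Adjustment could also be left to an analysis plan that is not shown. Here, however, the protocol itself fixes the tests, and they are unadjusted.

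**Conclusion.** The point holds as a loss of precision that can be recovered without new data. It applies fully to SF, mental health and QoL, where no between-arm test uses baseline and the only test that does is within arm. It applies in part to UL and PFS, where the factorial ANOVA uses baseline less efficiently than adjustment would.

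The residual variance falls by 9% to 49% for r from 0.3 to 0.7. At d = 0.5 and 83 per arm, that is 3 to 10 percentage points of power over the post-only t-test. Against the ANOVA interaction it is about 15 points at r = 0.3, 7 at r = 0.5 and 1 at r = 0.7. All these power figures rest on assumed r and d and on normal data. The document does not support a claim that the planned tests are biased or invalid. The change should be made, but the trial's validity does not depend on it.

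**What to change.** In Data analysis, make the main between-arm estimate for each outcome baseline-adjusted:

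- **UL and PFS:** ANCOVA on the post-intervention value with the baseline value as covariate. If leakage is skewed, analyse log(x + c), with the constant c stated in advance and the same transformation applied to baseline. A constant is needed because leakage can be zero (Primary outcome measure defines cure as below 1 g). A rank-based or ordinal adjusted model is an alternative.
- **SF, QoL, anxiety and depression:** ANCOVA with the baseline score, or a proportional-odds model with baseline as covariate if the scores are too skewed.
- **Reporting:** the adjusted effect with its 95% confidence interval, pooled over the imputations.
- **Existing tests:** keep the unadjusted post-score tests, if wanted, as supporting analyses. If the factorial ANOVA is kept, state that time is a repeated factor. Present within-arm change descriptively, and say that it is not evidence of a PEM effect.

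The cost is a change of analysis wording and one extra parameter per model. No visit, measurement or participant is added.
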